##### Sample Size for the Nested Neuroimaging Component

As per Desmond and Glover [90], a liberal threshold of α=.05 requires 24 participants (12 per group) to achieve an 80% power for the single-voxel level for typical activations. To control the error rate when conducting multiple comparisons, it is suggested that the number of participants should be doubled to maintain this level of power. On the basis of our Pediatric Concussion Assessment of Rest and Exertion and MRI study, of the 89 participants with concussion who provided consent, 13 were lost to follow-up, 3 had incidental findings, and 5 had excessive motion [91]. Considering a 20% attrition, a total sample size of 60 participants (30 per group) will be recruited.

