##### Imaging Measurements

*Imaging measurements* will be acquired within 72 hours of injury and during week 4 of the study on a subset of 60 participants. Each brain scanning session lasts 45 to 60 minutes and includes the following sequences: 3D T1-weighted anatomical scan to measure regional volumes and cortical thickness, resting-state functional MRI (rs-fMRI) to assess functional connectivity features or neural networks, arterial spin labeling to assess perfusion or cerebral blood flow, and magnetic proton spectroscopy in a single voxel in the anterior cingulate cortex to assess metabolite concentrations (ie, glutamate and gamma-aminobutyric acid). Table 3 lists the key imaging parameters.

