#### Neuroimaging Component: Nested Study

To acquire preliminary data on the association between the interventions and MRI metrics, per-protocol analyses will be conducted. A multivariable linear regression will be performed for each neuroimaging outcome, with age, sex, and handedness (for rs-fMRI) as covariates. If the groups differ at baseline on potentially confounding variables, such as attention-deficit or hyperactivity disorder, anxiety, medication, prior concussion, physical activity, and puberty, these variables will also be entered as covariates in the models. Per-protocol analyses will include only those participants who have adhered to the intervention.

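### The imaging sample size takes its 80% power from voxel-level activation, which this trial does not measure, and makes no allowance for the per-protocol restriction

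*Protocol article*

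**What the plan says.** The section Sample Size for the Nested Neuroimaging Component starts from a published figure: an alpha of .05, which it calls liberal, "requires 24 participants (12 per group) to achieve an 80% power for the single-voxel level for typical activations". For multiple comparisons, "it is suggested that the number of participants should be doubled to maintain this level of power". It then reports losses in the team's previous MRI study, where "of the 89 participants with concussion who provided consent, 13 were lost to follow-up, 3 had incidental findings, and 5 had excessive motion", applies 20% attrition and arrives at 60 participants, 30 per group.

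The outcomes are described elsewhere. Secondary Research Objectives names functional connectivity, cerebral blood flow and spectroscopy. Imaging Measurements lists "resting-state functional MRI (rs-fMRI) to assess functional connectivity features or neural networks, arterial spin labeling to assess perfusion or cerebral blood flow", together with metabolite concentrations from one anterior cingulate voxel and, from the T1 scan, regional volumes and cortical thickness. Table 4 lists anatomical, resting-state, arterial spin labeling and spectroscopy sequences only.

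The analysis is given under Neuroimaging Component: Nested Study: "A multivariable linear regression will be performed for each neuroimaging outcome, with age, sex, and handedness (for rs-fMRI) as covariates". That section describes the data as preliminary and confines the analysis to participants who adhered to the intervention.

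**The concern.** A power statement has to refer to an outcome that is measured and to the analysis that will be run. Here it refers to activation in an fMRI voxel. No task sequence is listed, so no activation will be measured, and no effect size or standard deviation for connectivity, blood flow, metabolites or structure enters the calculation. The figure also takes no account of the adherence restriction.

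What is at stake is how the imaging results can be interpreted. A reader of the sample size section would take it that the planned comparisons keep 80% power after multiplicity control, when the document gives no basis for that.

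**Working it through.** **1. Reproduce the plan's figure.** Inputs from the sample size section: base 24, multiplier 2, attrition 20%.

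24 × 2 = 48; 48 / (1 − 0.20) = 60. This matches the printed 60, so there is no arithmetic error.

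**2. Compare the basis with the outcomes.**

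| Listed measurement | Quantity | Voxel-level activation? |
|---|---|---|
| Resting-state fMRI | functional connectivity | no |
| Arterial spin labeling | cerebral blood flow | no |
| Spectroscopy | metabolite concentrations | no |
| T1 anatomical scan | regional volumes, cortical thickness | no |

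The shared term single voxel does not carry the figure over to spectroscopy. In the power statement it means one fMRI voxel showing activation; in the spectroscopy sequence it means the tissue volume in which metabolites are quantified.

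**3. What the printed numbers would imply for a between-arm comparison.** The section gives no effect size, SD or sidedness, so the starting 24 cannot be re-derived. As an assumption, take a two-sided two-sample t-test at alpha .05 with 80% power. The normal approximation is

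d = (1.960 + 0.842) × √(2/n), with n per arm.

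- n = 12: d = 1.14 (exact t: 1.20). One-sided, exact t: 1.05.
- n = 24: d = 0.81 (exact t: 0.83).

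**4. Usable scans before the adherence restriction.**

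- At the planned 20% loss: 60 × 0.80 = 48, or 24 per arm.
- If all three kinds of loss in the earlier study made a scan unusable: 13 + 3 + 5 = 21, and 21/89 = 23.6%. Then 60 × 68/89 = 45.8, about 23 per arm.

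**5. Apply the adherence restriction.** The fractions 70% and 50% are the protocol's own limits for adherence in Table 2. Applying them to the usable scans is an assumption.

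- 70%: 48 × 0.70 = 33.6 and 45.8 × 0.70 = 32.1, so 16 to 17 per arm.
- 50%: 48 × 0.50 = 24.0 and 45.8 × 0.50 = 22.9, so 11 to 12 per arm.

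**6. Detectable difference at 80% power (exact t, two-sided).** The last column divides alpha by 3, one test per modality named in the objective. It is illustrative; the document fixes no such scheme.

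| Set analysed | n per arm | alpha .05 | alpha .05/3 |
|---|---|---|---|
| All usable scans | 24 | 0.83 SD | 0.96 SD |
| All usable scans | 23 | 0.85 SD | 0.99 SD |
| 70% adherent | 17 | 0.99 SD | 1.16 SD |
| 70% adherent | 16 | 1.02 SD | 1.20 SD |
| 50% adherent | 12 | 1.20 SD | 1.41 SD |
| 50% adherent | 11 | 1.26 SD | 1.49 SD |

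**7. Power at assumed differences, alpha .05 uncorrected.** With 24 per arm: 40% at 0.5 SD and 77% at 0.8 SD. With 17 per arm: 29% and 62%. With 12 per arm: 22% and 47%.

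**The case against.** The strongest defence is that imaging is a secondary objective of a feasibility trial, its analysis is described as preliminary, and none of the five progression criteria in Table 2 depends on it. Sixty of the 70 participants are to be scanned in any case, so no scan or decision would change. All of this stands, and it limits the weight of the point. It does not rescue the power statement: a preliminary aim supports a statement of precision, not an 80% that belongs to another kind of measurement. Nor is this a detail left to a fuller document, since the article prints a rationale that conflicts with its own outcome list.

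Three stronger readings are tempting, and the documents do not support them.

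- A reader might infer that the sample size is miscalculated. It is not; 24 × 2 / 0.8 is 60.
- A reader might infer that the 20% attrition contradicts the earlier study's 23.6%. The text does not say that all 21 losses made scans unusable. If the 3 incidental findings stayed usable, 18/89 = 20.2% agrees with the printed rate. The difference is about two scans and is at most a side note.
- A reader might infer that a null imaging result will be taken as absence of effect, or that the figure will be used to size the definitive trial. Neither is stated. The Discussion says the future trial will assess quality of life and symptom burden.

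It is also fair to object that a detectable difference of 1.20 SD at 12 per arm is back-solved under an assumed test. It is, and it should not be presented as the cited source's own effect size.

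**Conclusion.** The point holds as a fault in the basis of the power claim. The printed 80% refers to voxel-level activation and applies to none of the planned imaging analyses, and no allowance is made for excluding non-adherent participants.

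Under the stated assumptions, the trial can detect about 0.83 to 0.85 SD if every usable scan is analysed, about 1.0 SD at 70% adherence and about 1.2 SD at 50%, before any multiplicity correction. These figures rest on a two-sided t comparison of equal arms, 80% power, and the same adherence among participants with usable scans as in Table 2. Those who return for the second scan may adhere better, which would move the result towards the first figure. Covariate adjustment could improve sensitivity somewhat; the document gives no figure from which to judge this. Because no effect size or SD is given for any imaging outcome, no single corrected sample size can be computed, and 60 is not shown to be too few for a preliminary aim.

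**What to change.** Keep the 60 scans. In Sample Size for the Nested Neuroimaging Component, delete the claim that 24 participants, doubled, preserve 80% power, and state the sensitivity of the planned analysis instead. Suggested wording:

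*Sixty participants will be scanned. We expect about 46 to 48 usable scan pairs (23 to 24 per arm) before restriction to adherent participants. Assuming a two-sided two-sample comparison at alpha .05 with 80% power, this number would detect a between-arm difference of about 0.83 to 0.85 SD. With 70% adherence (16 to 17 per arm) it would be about 1.0 SD, and with 50% (11 to 12 per arm) about 1.2 SD; all are larger after correction for multiple outcomes. The imaging analysis is exploratory and will be reported as adjusted between-arm differences with 95% confidence intervals.*

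If the team prefers to keep a power statement, it should name one imaging outcome, give its assumed effect and SD, and use the evaluable per-protocol number.

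The cost is one rewritten paragraph, with no added participants or scans. The downside is that the stated imaging sensitivity becomes less favourable.

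### The imaging sample size allows 20% attrition, but the earlier MRI study it quotes lost 21 of 89 (23.6%), so 60 recruited is expected to give about 46 analysable, not the implied 48

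*Protocol article*

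**What the plan says.** The section on the sample size for the nested neuroimaging component (Protocol article, Statistical Power) works in three steps.

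- **Base number.** Citing a published source, it states that "a liberal threshold of α=.05 requires 24 participants (12 per group) to achieve an 80% power" at the level of a single voxel.
- **Multiplicity.** To control error over multiple comparisons, "it is suggested that the number of participants should be doubled to maintain this level of power". The result, 48, is implied and not printed.
- **Attrition.** It turns to the group's own earlier concussion MRI study and reports that, "of the 89 participants with concussion who provided consent", "13 were lost to follow-up, 3 had incidental findings, and 5 had excessive motion". The next sentence reads: "Considering a 20% attrition, a total sample size of 60 participants (30 per group) will be recruited".

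The section does not say that only some of the three kinds of loss count towards attrition. It also does not say why 20% is used when the counts just listed give a different rate.

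**The concern.** The earlier study's losses are offered as the basis for the imaging attrition, and the 20% follows directly. A reader will take the 20% to summarise those counts. It does not: taken together they give a higher rate.

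The 48 is the number the section relies on to keep 80% power after allowing for multiple comparisons. If the loss rate the section quotes is the best guide to what will happen, recruiting 60 should be expected to fall slightly short of 48. The text as written implies that 60 secures it.

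**Working it through.** **Inputs, all from the imaging sample size section**

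- Base number: 24 in total, 12 per group
- Multiplicity factor: 2
- Attrition allowance: 20%
- Recruited: 60 in total, 30 per group
- Earlier study: 89 consented; 13 lost to follow-up, 3 with incidental findings, 5 with excessive motion

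**Step 1: reproduce the plan's figure.** Analysable target = 24 × 2 = 48. Recruited = 48 / (1 − 0.20) = 60. This matches exactly, so 48 is clearly the target behind the 60.

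**Step 2: loss rate in the quoted study.** 13 + 3 + 5 = 21, and 21/89 = 23.6%. The retained fraction is 68/89 = 76.4%. This assumes that the three categories are separate people and that each is lost to analysis.

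**Step 3: expected yield at that rate.** 60 × 68/89 = 45.8, about 46 in total or 23 per group. That is about 2 below the target.

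**Step 4: recruitment that would keep 48.** 48 / (68/89) = 62.8, so 63. By group, 24 / (68/89) = 31.4, so 32 per group and 64 in total.

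**Step 5: which losses are counted.**

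| Losses counted | Rate | Expected yield from 60 | Recruits needed for 48 |
|---|---|---|---|
| Follow-up only (13) | 14.6% | 51.2 | 57 |
| Follow-up + incidental findings (16) | 18.0% | 49.2 | 59 |
| Follow-up + motion (18) | 20.2% | 47.9 | 61 |
| All three (21) | 23.6% | 45.8 | 63 |

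The full sum gives the gap of about 2. Counting follow-up and motion alone comes very close to the plan's 20%, though it still needs 61 when rounded up.

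**Step 6: uncertainty.** The 95% Wilson interval for 21/89 is 16.0% to 33.4%, which contains 20%. If the true loss were exactly 23.6% and losses were independent, the analysable number from 60 would have mean 45.8 and standard deviation √(60 × 0.764 × 0.236) = 3.3. It would reach 48 or more with binomial probability of about 31%. If the true loss were exactly 20%, that probability would be about 58%.

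**The case against.** The strongest reply is that nothing has been miscalculated. Dividing 48 by 0.80 does give 60, and the section never states that 20% equals 21/89. On this view 20% is a rounded planning value. It lies inside the interval for the earlier study's rate and nearly equals follow-up plus motion losses. It also agrees with the roughly 20% that the Feasibility Objective section allows for the whole trial, from which the imaging participants are drawn.

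Part of this stands. The division is correct, and the fault lies in the input. The MRI study is not the only loss figure in the article. The 23.6% depends on counting all three categories without overlap, which is the natural reading but is not spelled out.

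The rest does not rescue the 20%. The whole-trial allowance covers loss to follow-up and withdrawals only, so it leaves nothing for scans excluded for motion or incidental findings. Leaving out the incidental findings would need a reason, because the section lists them beside the other losses, and none is given. That 20% is compatible with the data does not explain choosing a value below the quoted rate.

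A reader might go further than the article allows, in three ways:

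- **That the shortfall is certain.** It is an expectation based on another study's losses. Step 6 shows that 48 could still be reached.
- **That power falls to a particular figure, such as 78%.** That needs 48 to give exactly 80% power at a known significance level. The article attaches the .05 threshold to the 24, reaches 48 by a rule of doubling, and gives no effect size or standard deviation.
- **That the per-protocol rule enlarges this finding.** The analysis section does say "Per-protocol analyses will include only those participants who have adhered to the intervention", and the 60 makes no allowance for that. It is a separate matter that depends on an adherence rate not yet known, and it is not counted here.

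**Conclusion.** The point holds as a minor correction. The attrition allowance is lower than the loss rate quoted to introduce it, and no reason is given. At the quoted rate, 60 recruited is expected to give about 46 analysable participants (23 per group) where the power rule calls for 48 (24 per group).

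This rests on two assumptions: that the three loss categories do not overlap and each removes a participant from analysis, and that the earlier study's losses are a fair guide to this one. The consequence is small. The imaging component is secondary and meant to supply preliminary data, and none of the progression criteria in Table 2 depends on it.

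**What to change.** In the imaging sample size paragraph:

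- Restate the attrition as about 24% (21/89).
- Print the target of 48 (24 per group), and give the expected analysable number from 60 recruited as about 46 (23 per group).
- Say that this is slightly below the number the 80% power rule calls for, without attaching a revised power figure.

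If the sponsor prefers to keep 20%, the paragraph should say why it differs from the quoted losses, for example which categories are not expected to remove participants from analysis.

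The cost is a few words in one paragraph and a slightly less favourable expected number. Recruitment, design and analysis stay as they are.

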### Data Safety and Monitoring

#### Data Safety Monitoring Board

The independent data safety monitoring board (DSMB) will consist of 1 independent pediatric ED physician, 1 neuropsychologist who specializes in pediatric concussion, and 1 statistician who is not involved in the research study. In keeping with the StaRChild Health guidelines [92], the DSMB will, in collaboration with the trial steering committee, establish safety outcomes and termination rules before the start of the study. The DSMB will be immediately advised of severe adverse events, and they will meet in case a serious adverse event occurs. The DSMB will meet annually to review enrollment, study procedures, form completion, data quality, loss to follow-up, and interim safety results. Given the low-risk intervention and no intention to stop the trial for benefit or futility, only an annual meeting will be required. On the basis of negative data trends (increased symptoms) and adverse events, the DSMB may decide to meet earlier than planned and may request unblinding if deemed necessary.

#### Potential Harms

The safety outcomes include (1) severe worsening of symptoms identified on HBI reliable changes or (2) any symptoms requiring an unscheduled visit to the ED or primary care provider. If concussion symptoms worsen during the treatment to the degree that the participant requires an unscheduled visit to the ED or primary care provider, then symptoms will be considered as a possible adverse event. Symptoms could develop into an adverse event if they become unbearable and the patient needs immediate medical attention. Patients will report possible adverse events through REDCap reports, and their responses will be monitored by RAs. In the case of a possible adverse event, defined as the *worsening of symptoms requiring an unscheduled visit to the ED or primary care provider*, site investigators will be notified to determine if the event is linked to the treatment. If linked, the event will be monitored and the CHEO Research Ethics Board and DSMB will be notified.

### Ethical Considerations

This study was approved by the Research Ethics Board (protocol number 20/72X) of the CHEO Research Institute in August 2020. Authorization from Health Canada was granted in July 2022. The study will be carried out according to the principles outlined in the Declaration of Helsinki [93] and Good Clinical Practices, within the laws and regulations of the Tri-Council Policy Statement, and the institutional policies of the CHEO REB.

Before consent is sought, the study will be introduced, and its purpose will be explained verbally. The consent form will also present the purpose of the research, the procedures, potential risks and benefits, and the use and security of the data. Informed written consent will be obtained from the parents and participants deemed capable of consenting. Informed assent will be obtained from the participants deemed by the RA to be cognitively unable to provide informed consent.

The participants will be remunerated with a CAD $20 (US $15) gift certificate (eg, Tango) for completing surveys. Participants will receive an additional CAD $20 (US $15) gift certificate for completing the MRIs. The gift certificate will be sent electronically to their email address. They will also receive a parking voucher or vouchers for in-person meeting or meetings and a letter attesting that they have completed 20 hours of volunteer work (5 hours per week completing the intervention).

Participant information will be coded using study identification numbers. Research personnel will take all appropriate and customary steps to ensure that data remain secure and that patient privacy and confidentiality are maintained.

## Results

### Project Initiation

This trial is funded by the Children’s Hospital Academic Medical Organization Innovation Fund and the multidisciplinary team grant from the University of Ottawa Brain and Mind Research Institute. Recruitment began in October 2022, and data collection is expected to be completed by September 2024. Data collection and management is still in progress; therefore, data analysis is yet to be conducted.

### Dissemination

The results will be disseminated at international conferences and in scientific manuscripts to peer-reviewed journals. The main manuscript presenting the results of the primary objective will be published in a high-impact peer-reviewed journal. Furthermore, separate manuscripts will be written on the secondary objectives of the protocol, and these will also be submitted for publication in peer-reviewed journals. We plan to engage key stakeholder groups (eg, families, Parachute, Canadian Concussion Network, and Mobio Interactive) to ensure mobilization and uptake of the findings to end users to progress to the next step, that is, the efficacy trial.

## Discussion

First, we will use this study to examine the feasibility of our RCT methods, including delivering a DTx-containing MBI to participants who are acutely or subacutely concussed, and whether we can move to the efficacy trial. Second, to better inform our larger RCT, this study will allow us to estimate the effect sizes of QoL and the symptoms at 4 and 8 weeks after enrollment compared with those randomized to the control group (sham intervention). Third, we will use this study to assess whether MBI induces measurable brain-based effects, that is, examine whether the intervention modulates neuroimaging indicators such as functional connectivity. This trial will offer insight into a cost-effective way to manage pediatric concussion in the acute and subacute phases of injury. This study will help support the development of a future full-efficacy trial to assess the effectiveness of the intervention in increasing QoL and decreasing the concussion symptom burden.

The development of an intervention to increase adaptive interpersonal qualities in acute settings is important for reducing the risk of PSAC. Formal in-person MBIs such as mindfulness-based stress reduction have been shown to increase perceived self-efficacy and teach positive acceptance of change [13]. However, these interventions may not be suitable for a youth population with acute concussion as they are costly and not easily accessible. A brief web-based MBI with guided meditation had positive effects on anxiety, negative mood, perceived stress, and attention in different clinical populations [24-27]. Furthermore, a 3-week RCT using the DTx MBI within *AmDTx* increased stress resilience and attentional control in university students self-described as experiencing mild anxiety [27]. The customization of a novel MBI, designed in collaboration with MBI therapists, patients, and Mobio Interactive, will bring a required concussion treatment into the homes of all patients, with the goal of increasing adaptive skills and cognitive performance, promoting neural recovery, and reducing the risk of PSAC. If found to be effective, DTx MBI holds promise as an accessible and low-risk preventative treatment for youth at risk for prolonged postconcussion symptoms and sequelae.

